### Design

A randomized, controlled, three-arm, large-scale trial to compare two true EA groups (strong EA and weak EA) with a sham EA group will be undertaken in this study [8]. Four hundred and fifty KOA patients will be recruited from the following six hospitals: the Combined Traditional Chinese and Western Medicine Hospital Affiliated to Huazhong University of Science and Technology, The Third Hospital of Wuhan, Central Hospital of Wuhan, Union Hospital Affiliated to Tongji Medical College of Huazhong University of Science and Technology, Wuhan Hospital of Traditional Chinese Medicine, and The Fifth Hospital of Wuhan. Patients will be randomized in a ratio of 1:1:1 to the strong EA group, weak EA group and sham EA group. After submitting informed consent and being randomized, patients will receive 10 sessions of EA treatment over a period of 2 weeks, with a treatment frequency of 5 sessions per week. Each session will last 30 minutes. Patients will be asked to accept assessments at baseline, as well as at the end of the first and second weeks of the treatment phase. Time points and groups are shown in Figure 1.

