### Outcome assessments

#### Primary outcome measurements

The primary outcome measurements are the Visual Analog Scale (VAS), DNIC function and the Western Ontario and McMaster Universities Osteoarthritis Index (WOMAC).

VAS is an internationally recognized pain scale. It is a 100-mm line ranging from 0 (no pain) to 100 (pain as bad as it could be) [14].

The prediction of chronification of acute pain can be indicated by DNIC function, which means that pain elicited by a noxious stimulus applied to a given body site can be attenuated by application of a conditioning noxious stimulation to another, even distant body region [15]. DNIC function will be measured according to the procedure shown in Figure 3. On the Ashi-point (pain spot) of the affected knee, the research assistant will apply a 180-g von Frey filament (bending it so that it forms a 45-degrees angle with the skin) three to five times within a 1-cm-diameter circle (Figure 3A). The patients will be asked to rate the intensity of pain as VAS1 [5], which is the induced mechanical pain score of the affected knee. Then, the patients will be asked to immerse the contralateral hand, including the wrist, into nociceptive cold water (10 to 12°C) for 1 minute and rate the intensity of the pain induced by the 180-g von Frey filament on the Ashi-point as VAS2 (Figure 3B). For healthy people, the conditioning cold noxious stimulation can activate the descending inhibitory system of the spinal cord. VAS2 is used to detect the induced mechanical pain score of the affected knee after conditioning with the cold noxious stimulation on the contralateral hand. Finally, DNIC function will be assessed by measuring the difference in pain ratings before and after immersion (DNIC = (VAS1-VAS2)/VAS1). Thus, the decreased ratio in pain scores of the affected knee before and after the cold noxious stimulation of the hand is the DNIC function [2,16].

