### Data analysis

Data with normal distribution will be presented as means ± SEM. We will use a one-way analysis of variance (ANOVA) or a two-way ANOVA to determine the overall effect of EA. The Post hoc test (Newman Keuls test) will then be used to determine the statistical differences among individual groups. A *P* value of less than 0.05 will be considered statistically significant. Data showing an abnormal distribution will be analyzed by the Wilcoxon signed-rank test.

In order to determine which EA intervention is the best for each of the different stages of KOA, patients in the three EA groups will be further divided according to four different stages of KOA:The acute pain stage group. The pain of KOA has been ongoing for less than 6 months.The early chronic pain stage group. The pain of KOA has been ongoing for 6 months to 3 years.The medium-term chronic pain stage group. The pain of KOA has been ongoing for 3 to 5 years.The advanced chronic pain stage group. The pain of KOA has been ongoing for more than 5 years (Figure 4A).

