**Figure 4 Fig4:**
[figure not shown]
**Data analysis chart. A**. We will divide the three electroacupuncture (EA) groups into four different stages to screen separately for the stage where the EA intervention will be most effective. **B**. We will divide all patients into four stages and compare the effects of strong, weak and sham EA separately within the different stages. The Visual Analog Scale (VAS), diffuse noxious inhibitory control (DNIC) function, Western Ontario and McMaster Universities Osteoarthritis index (WOMAC), Numerical Rating Scale (NRS), Emotional Scale (ES), Present Pain Intensity (PPI), range of motion (ROM) will be measured by the procedure outlined in the chart.

The effect of EA on the different stages of KOA will be observed, and the stage with the best response to EA intervention will be discussed. Furthermore, in yet another comparison, we will divide all patients into the four stages and then compare the effects of the strong, weak and sham EA groups within the different stages separately (Figure 4B).

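### The only test named for non-normal data, the Wilcoxon signed-rank test, cannot compare three independent arms, so a primary outcome judged non-normal would have no valid between-arm analysis

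*Protocol article*

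**What the plan says.** The design is parallel-group. The Design section sets out to "compare two true EA groups (strong EA and weak EA) with a sham EA group" and continues: "Patients will be randomized in a ratio of 1:1:1 to the strong EA group, weak EA group and sham EA group". It mentions no matching or crossover.

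The Data analysis section then gives two routes.

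- **Normal data:** "We will use a one-way analysis of variance (ANOVA) or a two-way ANOVA to determine the overall effect of EA", followed by "The Post hoc test (Newman Keuls test) will then be used to determine the statistical differences among individual groups".
- **Non-normal data:** "Data showing an abnormal distribution will be analyzed by the Wilcoxon signed-rank test".

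The second route names the only non-parametric method in the article. It is not limited to particular outcomes or to change within an arm. The same section, after Figure 4, plans to "compare the effects of the strong, weak and sham EA groups within the different stages separately", which is again a comparison of independent groups.

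The outcomes affected include the primary ones: "The primary outcome measurements are the Visual Analog Scale (VAS), DNIC function and the Western Ontario and McMaster Universities Osteoarthritis Index (WOMAC"). DNIC function, which also drives the sample size, is calculated as "DNIC = (VAS1-VAS2)/VAS1".

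**The concern.** The non-parametric sentence comes directly after the ANOVA and post hoc sentences and serves as their substitute when normality fails. It therefore has to answer the same question, whether the arms differ. A signed-rank test cannot do that, because it asks whether paired differences, or one sample, are centred on zero.

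The stake is the randomised comparison. The Discussion section says that sham EA is there to rule out a placebo effect. A before-after test inside each arm mixes any treatment effect with natural course, regression to the mean and placebo response, so significance in the EA arms would not separate EA from sham. The branch could reach DNIC, the outcome on which the trial is sized.

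**Working it through.** **1. What the test needs and what the design offers.** The protocol produces paired data in two places only: the same patient at baseline and at the end of week 1 or 2, and the same patient's VAS1 and VAS2. Strong, weak and sham EA patients are different people. So are patients in different KOA stages. The signed-rank test therefore fits none of the planned group comparisons.

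**2. The two ways the sentence could be carried out.**

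(a) *Before against after, arm by arm.* This can be computed but does not compare arms. Illustration (assumed distribution, not from the protocol): three arms with identical skewed changes, exponential with SD 20 and mean improvement 10, and 127 patients per arm (150 × 0.85 = 127.5, rounded down). Over 2,000 runs:

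| Test | Rejection at 5% |
|---|---|
| Signed-rank, each arm | 99.6% to 99.8% |
| Signed-rank, all three arms together | 99.1% |
| Kruskal-Wallis across arms | 5.5% |

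The arms do not differ. Kruskal-Wallis reports this at close to its nominal error rate; the signed-rank results carry no information about it.

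(b) *Pairing patients across arms.* The pairing is arbitrary. On one fixed simulated data set, re-ordering the patients moved the p-value from 0.019 to 0.51, while the rank-sum test gave a single value, 0.040. With unequal arms (127 and 124) the test cannot be computed.

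**3. How readily each arm would be significant on the plan's own figures.** The Sample size section assumes DNIC gains of 30%, 20% and 15%, 90% power, a 5% level and 15% attrition. It gives no SD, so 150 per arm cannot be reproduced directly. Read as means in a one-way ANOVA, the SD can be solved for:

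- Mean of the three gains: (30 + 20 + 15)/3 = 21.67.
- Sum of squared deviations: 69.44 + 2.78 + 44.44 = 116.67.
- Noncentrality: 127 × 116.67/SD². Power is 90% (noncentral F, 2 and 378 degrees of freedom) at SD = 34.1.

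Powering a single pair instead implies an SD of 12.3 (20 against 15), 24.6 (30 against 20) or 36.9 (30 against 15). The SD is therefore an assumption.

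With an SD of about 34 and 127 patients, the within-arm signed-rank test rejects as follows (normal gains simulated):

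| True mean gain in the arm | Rejection rate |
|---|---|
| 15 points (the plan's sham assumption) | over 99% |
| 5 points | about 37% |
| 0 points | about 5% |

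Sham significance is nearly certain only if sham patients gain what the plan assumes.

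**4. Is the branch realistic for DNIC?** The ratio cannot exceed 1, can fall well below zero when VAS1 is small, and is undefined at VAS1 = 0. With assumed inputs (VAS1 normal with mean 50 and SD 20, inhibition 10 ± 10 mm, both ratings kept within 0 to 100), median sample skewness at n = 127 was about +0.5 to +0.6. A Shapiro test rejected normality in 74% to 97% of runs, depending on the smallest VAS1 admitted. The departure is moderate, but a formal normality test would often detect it.

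**The case against.** The strongest reply is that the sentence is a fallback. The main route, ANOVA with pairwise follow-up, does compare arms, and no normality test or threshold is stated, so the article alone cannot show that any primary outcome will leave that route. This stands, and it makes the consequence conditional.

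A second reply is that signed-rank is a slip for rank-sum. That is possible, but the text says signed-rank. A two-sample rank-sum test would also leave the three-arm overall test and the control of pairwise error unspecified, so the sentence would still need changing.

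A third is that such detail belongs in an analysis plan. That would excuse silence, but here a test is named and it is the wrong one.

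Three stronger readings are tempting and not supported:

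- *The DNIC ratio is bound to be severely skewed.* The protocol gives no distribution of VAS1 or VAS2. Under the assumed inputs above the skewness is moderate, and its size and sign depend on how many near-zero VAS1 values are admitted. ANOVA kept its size under those inputs (4.8% and 5.5% rejection under the null).
- *Every arm will show a significant improvement.* This needs a real sham gain of about the assumed 15 points and an SD near 34, and the protocol states no SD. That illustration also uses normal gains, which under the plan's own rule would go to ANOVA.
- *The trial has no valid between-arm analysis.* This is true only of outcomes sent down the non-normal route.

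**Conclusion.** The sentence is wrong as written. For any outcome judged non-normal, the protocol names a test that cannot compare the three randomised arms and offers no other. This conclusion follows from the design and the named test; it depends on no SD or simulated distribution.

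Its practical size depends on whether a primary outcome takes that branch, which is realistic for DNIC but not established. If it does, the randomised comparison for that outcome is lost, and within-arm significance, sham included, becomes likely to the extent that all arms improve. The rejection rate above 99% is an illustration resting on a 15-point sham gain and an SD of about 34; at a 5-point gain it is about 37%.

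**What to change.** Replace the sentence before treatment allocation is revealed for analysis. Suitable content: outcomes judged non-normal are compared across the three arms with the Kruskal-Wallis test, followed by pairwise Wilcoxon rank-sum (Mann-Whitney) tests with a named multiplicity adjustment; the signed-rank test is used only to describe change within an arm. The same rule should cover the comparisons within KOA stages. If a stratified rank test is preferred, it should use the actual randomisation strata. The Randomization and blinding section says the randomisation is stratified but names no factor, so centre should not be presumed.

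An acceptable alternative is one pre-specified between-arm model with robust standard errors for each outcome. It would also avoid letting the observed distribution choose the test, but it is not needed to correct this error.

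The cost is one sentence, with no change to data collection or patient burden. On precision, if ANOVA needs 127 evaluable patients per arm, Kruskal-Wallis needs 127/0.955 = 133 for normal data and at worst 127/0.864 = 147 for location shifts (large-sample efficiencies). Allowing for 15% attrition, that is 133/0.85 = 157 to 147/0.85 = 173 randomised per arm. With skewed data the rank test may need fewer patients than ANOVA.

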**Figure 4 Fig4:**
[figure not shown]
**Data analysis chart. A**. We will divide the three electroacupuncture (EA) groups into four different stages to screen separately for the stage where the EA intervention will be most effective. **B**. We will divide all patients into four stages and compare the effects of strong, weak and sham EA separately within the different stages. The Visual Analog Scale (VAS), diffuse noxious inhibitory control (DNIC) function, Western Ontario and McMaster Universities Osteoarthritis index (WOMAC), Numerical Rating Scale (NRS), Emotional Scale (ES), Present Pain Intensity (PPI), range of motion (ROM) will be measured by the procedure outlined in the chart.

The effect of EA on the different stages of KOA will be observed, and the stage with the best response to EA intervention will be discussed. Furthermore, in yet another comparison, we will divide all patients into the four stages and then compare the effects of the strong, weak and sham EA groups within the different stages separately (Figure 4B).

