## Background

Knee osteoarthritis (KOA) is one of the most common types of osteoarthritis and often occurs in older adults [1]. Patients with KOA often suffer from pain around the joints and have a high risk of chronification of acute pain. Chronification of acute pain means that persistent acute pain without positive intervention can damage the nervous system and then change into intractable chronic pain [2]. In recent years, a series of clinical randomized controlled trials indicated that electroacupuncture (EA) is effective for treating various painful diseases such as KOA in the acute phase but did not solve the clinical problems of the chronification of acute pain of KOA [3].

The concept of diffuse noxious inhibitory controls (DNIC) has attracted particular attention in the past decades, which means under normal conditions, pain can be attenuated by a conditioning noxious stimulus to a remote body region [4]. DNIC function is now regarded as a reliable indicator for predicting the risk of chronic pain [5,6]. DNIC function in KOA patients has been shown to gradually decrease with the development of chronic pain [7]. Thus, we hypothesized that the process of chronification of acute pain may be related to gradually impaired DNIC function, and EA may prevent the occurrence of chronification of acute pain by improving DNIC function.

The aim of this study is to explore whether EA can reverse impaired DNIC function by reducing the pain of KOA during the process of chronification of acute pain. Moreover, we will screen for the best EA therapeutic regimen, which will include optimizing the intensity of the current used in the EA stimulation and determining the best stage for effective EA intervention using a randomized controlled clinical trial.

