## Discussion

The aim of this trial is to use EA intervention to inhibit chronification of the acute pain of KOA by reversing the damage to the DNIC function. Completion of this trial will help to identify whether EA with high-intensity current (strong EA) is more effective than EA with low-intensity current (weak EA) and whether EA applied at an early stage of KOA will be more effective than that at a later stage of KOA.

We will establish two treatment groups and one control group in this randomized controlled trial. Since the primary consideration of this trial is to clarify whether EA is effective in preventing chronification of the acute pain of KOA, we will use sham EA as a control to rule out the placebo effect. In the sham EA group, acupuncture needles are shallowly inserted into non-acupoint locations to rule out the effect of acupoint. Because most of the KOA patients are familiar with the sensation of EA, they could realize that it is the sham EA if they cannot feel any current from the apparatus. Therefore, we will use a low intensity of electrostimulation to exclude a placebo effect.

Acupoints of EX-LE5, ST34, ST35, and SP10 are located around the knees, which have been regarded as the most common and effective acupoints for use in treating KOA in many high-quality trials [11,21]. Since 2 Hz is the optimized EA frequency for the relief of inflammatory pain, we chose the 2 Hz as the best frequency of EA to treat KOA in this study [22].

DNIC involves supraspinal structures, modulates the transmission of nociceptive signals and is another pain perception methodology recently used to study pathophysiology of various pain disorders because it reflects the function of the endogenous pain system [23,24]. This pain-modulating process is the neurophysiological basis for the well-known phenomenon where ‘pain inhibits pain’ from remote areas of the body [5]. The continuous pain input will impair the DNIC function and then decrease antinociceptive activity from the supraspinal structures, which may result in the occurrence of chronic pain [25]. Numerous studies have demonstrated that DNIC may be involved in the analgesic mechanism of acupuncture [26,27]. However, no study has used DNIC function to screen for the best EA intensity and for the best stage of chronification of acute pain for an effective EA intervention.

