To screen for the optimal intensity of EA for improving DNIC function, the effect of strong EA and weak EA will be compared. EA with low-intensity current (less than 1 mA) has been demonstrated to mainly excite large fibers (Aβ fiber), which may not activate the DNIC function [28]. Instead, this innocuous stimulation may only exert an analgesic effect through the spinal mechanism of gate control theory [29]. In contrast, EA with high-intensity current (more than 2 mA) excited thin fibers (A δ and/or C fibers) and may activate DNIC function [30]. Thus, we will compare the effect of strong EA and weak EA on repairing impaired DNIC function to screen for the best EA intensity to prevent chronification of the acute pain of KOA. We hypothesize that both strong EA and weak EA may have some pain-reducing and inflammation-relieving effects, which will be assessed with VAS, WOMAC, NRS, ES, PPI and ROM. However, strong EA may be more effective in improving DNIC function and, thus, in reversing the chronification of acute pain [28].

Moreover, we also will try to determine the best stage of KOA for EA intervention. DNIC function is the function of the endogenous analgesic system [16]. In other words, the process of gradually decreased DNIC function is also the process of transforming acute pain to chronic pain. In this process, if patients receive EA intervention as soon as possible, it is possible that the chronification of pain in KOA patients will be prevented. However, at the later stages of chronic pain, peripheral and central sensitization will likely irreversibly damage the endogenous analgesic system function and completely impair DNIC function [2]. At that point, EA may not be as effective. So, we will further divide the KOA patients according to the stage of the disease. We hope to find the best stage for the use of EA to reverse the impaired DNIC function and prevent the chronification of acute pain.

This project will not only increase knowledge on the effects of treating KOA with EA, but also may contribute a solution to the difficult problem of the chronification of acute pain, and promote the clinical application of EA analgesia.

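### The stated stage analyses do not test whether the EA effect differs between pain-duration stages, so the best stage they name may reflect prognosis or chance

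*Protocol article*

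**What the plan says.** The protocol article makes stage a stated aim. The Discussion says the completed trial will help to show "whether EA applied at an early stage of KOA will be more effective than that at a later stage of KOA", and adds: "We hope to find the best stage for the use of EA to reverse the impaired DNIC function and prevent the chronification of acute pain".

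Data analysis sets stage by duration of pain: under 6 months, 6 months to 3 years, 3 to 5 years, and over 5 years. It says "patients in the three EA groups will be further divided according to four different stages of KOA"; the three groups include sham. Two analyses follow, described in the Figure 4 legend and the text after it:

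- **Figure 4A:** each arm is split by stage "to screen separately for the stage where the EA intervention will be most effective", and "the stage with the best response to EA intervention will be discussed".
- **Figure 4B:** all patients are split by stage, in order to "compare the effects of strong, weak and sham EA separately within the different stages".

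For testing, the section names a one-way or two-way ANOVA, tied to the overall effect of EA, and then: "The Post hoc test (Newman Keuls test) will then be used to determine the statistical differences among individual groups". The threshold is P<0.05. No arm-by-stage interaction and no between-stage comparison of the EA-minus-sham difference is stated. The chart itself was not available, so this rests on its legend and the surrounding text.

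**The concern.** Whether EA works better early than late is a question of effect modification: is the strong-minus-sham (or strong-minus-weak) difference larger in one stage than in another? An answer needs a controlled contrast in each stage and a comparison of those contrasts. Figure 4A lacks the first and Figure 4B stops before the second.

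In 4A the stages are not randomised groups. The Background states that "DNIC function in KOA patients has been shown to gradually decrease with the development of chronic pain", and the Discussion expects late-stage damage that may be irreversible. On the article's own account, the stages can therefore be expected to differ in prognosis whichever treatment is given. A ranking of stages inside one arm attributes those differences to EA. The Discussion says sham is there to rule out a placebo effect, but 4A does not use it for that.

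At stake is a headline conclusion, the stage at which EA should be used. The overall randomised comparison of the three arms is not affected.

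**Working it through.** **Inputs from the article (Sample size):** mean DNIC increases of 30, 20 and 15 for strong, weak and sham; 150 per arm; 15% attrition; 5% level; 90% power. I read the increases as mean changes in percentage points.

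**Not given, so assumed:** the SD and the stage shares. The 150 per arm cannot be reproduced without an SD, so I solved for the SD that gives 90% power.

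1. Evaluable per arm: 150 × 0.85 = 127.5, taken as 127.

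2. Implied SD:
 - Three-arm ANOVA. Sum of squared deviations of 30, 20, 15 about their mean = 116.7. Power is 90% when 127 × 116.7 / SD² ≈ 12.75, so SD ≈ 34.
 - Strong vs sham: 15 × √(127/2) / (1.960 + 1.282) = 36.9.
 - Strong vs weak: 10 × √(127/2) / (1.960 + 1.282) = 24.6.
 - Working range: 25 to 37 points, with 34 as the central value.

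3. Cell size with four equal stages: 127/4 ≈ 32 per arm per stage.

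4. **Figure 4B with the same true effect in every stage.** ANOVA plus Newman-Keuls was simulated with 32 per cell. The chance of a mixed result (some stages significant, others not) is 1 − p⁴ − (1−p)⁴, where p is the chance of significance in one stage.

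| SD (points) | Strong vs sham significant in a stage | Mixed result across four stages |
|---|---|---|
| 25 | about 52% | about 87% |
| 34 | about 29% | about 74% |
| 37 | about 24% | about 67% |

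 Check at SD 34: 1 − 0.29⁴ − 0.71⁴ = 1 − 0.007 − 0.254 = 0.74. The three-arm F test alone gives mixed results in 74% to 85% of trials with equal stages over this SD range, and in 75% to 90% if the stages hold 10/30/25/35% of patients.

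5. **Size of the apparent best stage at SD 34.** SE of strong minus sham in one stage = 34 × √(2/32) = 8.5. The expected largest of four such estimates is 15 + 1.03 × 8.5 ≈ 24, against a true 15. The expected gap from best to worst stage is 2.06 × 8.5 ≈ 17.5, larger than the effect itself.

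6. **No EA effect at all:** 1 − 0.95⁴ = 18.5% chance that at least one of the four stage tests is significant, per outcome and visit.

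7. **Figure 4A.**
 - No real stage difference: 1 − 0.95³ = 14.3% chance that at least one of three arms shows a significant stage difference, per outcome.
 - Stages differ only in prognosis and EA works equally in all (SD 34, simulated). With an assumed spread in DNIC change of 15 points across stages, at least one arm shows a stage difference in about 66% of trials; with 30 points, in about 99.9%. The sham arm alone does so in about 31% and 89%.
 - An arm-by-stage interaction test on the same data stays near 5% (4.3% to 5.1%).

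8. **What the interaction can detect.** SE of the difference between two stages in strong minus sham = 8.5 × √2 ≈ 12. Detectable with 80% power: 2.80 × 12 ≈ 34 points, over twice the assumed overall difference of 15.

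**The case against.** The best defence concerns Figure 4B. Data analysis gives one purpose of the staging as finding which form of EA is best for each stage. For that purpose, comparing randomised arms within a stage is the right contrast, and it yields a usable strong-minus-sham estimate per stage. This stands. What remains is the other question, early against late, which four separate comparisons do not test.

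A reader might infer that the plan will declare EA effective in significant stages and ineffective in the rest. No such rule is written. The point is only that 4B offers no formal comparison between stages.

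A reader might also blame regression to the mean. That is not shown: stages are set by pain duration, and the eligibility criteria set no VAS or DNIC threshold. The article supports differences in prognosis, not this mechanism.

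The two-way ANOVA could include stage, and a condensed article may leave its factors to the analysis plan. But the text ties it to the overall effect of EA and describes both stage analyses as separate. The wording is also partly tentative (screening, observing, discussing, hoping), and the sample size concerns the arms only. This makes an exploratory label natural, but the Discussion still presents early versus late as a question the trial will help to answer.

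Finally, the mixed-result figures assume a uniform effect, whereas the article predicts less benefit late. The uniform case shows how readily the stated analyses produce an apparent stage pattern when none exists. It does not show that none exists.

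**Conclusion.** The concern holds in this form: the article asks whether EA works better at an early stage and fixes two analyses, neither of which tests it. Figure 4A is an uncontrolled ranking of non-randomised groups. Figure 4B is sound within each stage but silent between stages.

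Under a uniform true effect, four equal stages and a back-solved SD of 25 to 37 points, about 67% to 87% of trials would show significance in some stages and not in others. At SD 34 the best-looking stage would show about 24 points against a true 15. These figures depend on an SD and stage shares that the article does not give, and the 66% and 99.9% figures for 4A also depend on an assumed prognostic gap.

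Two stronger readings are not supported. One is that the stage named will be mostly noise: with no EA effect and no prognostic difference, the error rates are 18.5% (4B) and about 14% (4A), and the true pattern across stages is unknown. The other is to count here that a 2-week DNIC change cannot show prevention of chronic pain. That concerns the endpoint of the whole trial and adds nothing to this point.

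**What to change.** Fit one model for DNIC with arm, stage (or pain duration as a continuous variable), the arm-by-stage interaction and baseline DNIC. Base any statement about the best stage on the interaction. Report strong-minus-sham and strong-minus-weak differences with 95% CIs for each stage, keep Figure 4A as description only, and label the stage results exploratory.

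This takes revised analysis text and a redrawn Figure 4, using data already planned. The cost is a more modest stage conclusion: the interaction has low power, so a non-significant result would not show that the stages respond alike.
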